### Description of the randomization

A simple randomization system will be used, in which the selected patients will be randomly assigned by a computer program in a 1:1 ratio to one of two study arms: the intervention arm (dissection route from the IMV to the IMA) and the control arm (dissection route directly to the IMA).

### Blinding

Neither the patient nor the urologist performing the sexual and urinary function study will have access to any surgical data; nor will they know which arm of the study the patient belongs to.

### Trial interventions

Patients who meet the inclusion criteria and sign the informed consent document will be referred to the urologist for functional study after 8–10 weeks of neoadjuvant treatment, before surgery (Fig. 2).

**Fig. 2 Fig2:**
[figure not shown]
Proposed study schedule

The study consists of: a) an anamnesis with medical and psychosexual history; b) total testosterone level (ng/dL); c) Erection Hardness Score (EHS) [19]; d)IIEF-5 [18];e) I-PSS [22]; f)ICIQ-SF [21]; g) the European Organization for Research and Treatment of Cancer Quality-of-Life questionnaire (EORTC-QLQ C30) [27]; h) Doppler ultrasound of the penis; i) Urodynamic study.

For the Doppler ultrasound of the penis, a baseline study will be carried out to assess the ultrasound structure of the scrotal wall, both corpora cavernosa and the corpus spongiosum, the presence of calcifications or plaques of fibrosis, and their location. Subsequently, 15 mg of prostaglandin E1, a vasodilator agent that induces erection,will be applied to one of the corpora cavernosa (the sidechosen for the injection is irrelevant). After 20 min of the application the ultrasound provides dorsal and transversal measurements during the initial phases, and oblique-longitudinal measurements once tumescence begins, of the diameter of both cavernous arteries, their peak systolic flow velocity (cm/s) and their flow velocity at the end of diastole (cm/s) [28].

For the urodynamic study a flowmetry will be performed, recording: maximum urine volume (mL), maximum flow (mL/s), average flow (mL/s), and urination time (s)) and subsequently an ultrasound evaluation of postvoid residue (mL) [20].

Subsequently, patients undergo surgery after being randomly assigned to one of the two study arms. Before surgery, all patients will undergo mechanical colon preparation with antibiotic and thromboembolic prophylaxis, in accordance with the center’s protocol.

### Surgical technique

The surgery performed will be TME, using laparoscopic low anterior resection (LAR) approach or transanal TME (TaTME) [29], combining a laparoscopic approach and Transanal endoscopic operation (TEO).

The surgery is performed only by 5 surgeons, who are part of the colorectal unit. All of them experts in laparoscopic surgery and they have training on both techniques (intervention and control arm).

The surgery is performed laparoscopically with the patient in the Lloyd-Davies position. If release and mobilization of the splenic angle is necessary the Melani technique is applied [15], with the subsequent dissection of the IMA according to the randomization schedule, as follows:Control group, with direct dissection of the IMA. Opening of the mesosigma peritoneum, laterally separating the SHP and hypogastric nerves. Visualization and preservation of the ureter, left primitive iliac vessels and the left gonadal vessels, and maintaining Gerota’s fascia intact. High ligation of the IMA is performed about 1.5-2 cm from its origin in the aorta. The medial-to-lateral dissection proceeds, as far as the dissection of the splenic angle mobilization;Intervention group, with dissection of the IMV to the IMA. Release of the splenic angle is followed by medial to lateral dissection from the IMV to the IMA, and a high ligation is performed about 1.5-2 cm from its origin in the aorta. Subsequently, the dissection follows the plane of the retroperitoneum from cranial to caudal and medial to lateral as far as the mesosigma.

The surgery continues with the following standardized steps: opening of the left Told’s Fascia; mesorectal dissection immediately posterior to the superior rectal artery, following the plane anterior to the presacral parietal fascia; bilateral dissection, avoiding traction and blunt dissection that might damage the nerves or the integrity of the mesorectum; the anterior dissection is performed after completing the posterior dissection as far as the pelvic floor, leaving the Denonvilliers fascia intact, and following the avascular plane.

In the case of laparoscopic LAR, a Pfannenstiel incision is made toextract the specimen with the subsequent mechanical end-to-end colorectal anastomosis with EEA™ Auto suture 28 (Covidien™, Dublin, Ireland).

In transanal TME [29],TEO equipment is used (Karl Storz GmbH, Tüttlingen, Germany), and a pouch is made to close the distal rectum at least 1 cm below the visualization of the lesion. The area of the sectionis marked 1 cm from the pouch and transanal dissection of the mesorectal is carried out until reaching the dissection performed by laparoscopy. The lateral anterior dissection continues, leaving the Denonvilliers fascia intact.

In the case of an end colostomy is required, a colostomy orifice is performed in a previously marked site, sectioning the proximal colon with a scalpel and performing an end colostomy, with placement of a prophylactic mesh using the modified Sugarbaker technique [30, 31].

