**Fig. 1 Fig1:**
[figure not shown]
Outline of the pelvic autonomic nerves and their target organs

**Table 2 Tab2:** Areas with risk of lesion in the main autonomic nerves, and their effects

Nerve injured		Area of risk	Urinary dysf.	Sexual dysf.
SHP (sympathetic)		Dissection and ligature of IMA	Stress urinary incontinence	Retrograde ejaculation
Hypogastric nerves		Posterior dissection		Alteration in ejaculation (no alteration erection)
Splanchnic nerves (parasympathetic)		Rare in TME In radical lymph node dissections	Neurogenic bladder	Men: alteration erection Women: Dyspareunia
IHP (mixed)		Lateral dissection	Incontinence Difficulty voiding	Problems with ejaculation and erection
- IHP one-sided			Difficulty voiding	Men: Ejaculation and erection problems Women: Problems with genital lubrication
- IHP two-sided			Bladder denervation	Men: impotence Women: dyspareunia and ↓ability to reach orgasm
Neurovascular bundle of Walsh and cavernous nerve		Anterior dissection		Men: impotencia and erectile dysfunction Women:dispareunia and reduced genital lubrication
Pudendo nerve and levator ani		Perineal stage of Miles APR	Urinary incontinence	Sexual sensorial impotence

Recently, Melani [15] described a new laparoscopic approach for the release of the splenic flexure, in which a dissection of the mesenteric vessels is performed from the inferior mesenteric vein (IMV) to the IMA. This route presents a dissection plane that follows the anatomical peritoneal sheets of the retroperitoneum and improves the visualization of the pelvic autonomic nerves from their origin. Compared with the standard approach to the inferior mesenteric vessels (i.e., directly on the IMA), we believe thatthe approach from the IMV to the IMA will improve nerve preservation and thus reduce the incidence of sexual and urinary dysfunction.

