#### Surgical

Type of surgical technique (LAR, NOTES-hybrid), surgical time.

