Quality of life in our patients is defined by the need for an ostomy orby the presence ofsexual and urinary dysfunctions. Data on these dysfunctions are generally compiled through the use of questionnaires, which all present subjective limitations. As described above, sexual dysfunction is the difficulty at any stage of sexual intercourse (including desire, arousal, orgasm and resolution) that prevents the individual or their partner from enjoying sexual activity [5]. As detailed in the material and methods section, we have followed the indications of the EAU *guidelines (2017)* for the study of sexual dysfunction. The reason for adding the Doppler ultrasound study is to evaluate the cavernous arteries and their spectral evolution, in order to record objective parameters of induced erection and thus to identify the cause of the erectile dysfunction [17]. In addition, there is no reference in the literature of the study of SD in TME with the Doppler and that will give us objective data about it. Clearly, anxiety, psychological strain and any adrenergic stimulus may lead to false positive results, but with the exception of these cases, an altered result can be attributed to a neurogenic cause of erectile dysfunction in patients with a history of nerve damage [36]. Urinary dysfunction is defined as any alteration in the correct functioning in the storage or periodic voiding of urine, either in isolation or simultaneously. The tests used in the study are, once again, the ones recommended in the EAU *guidelines*; however, the only method able to objectively evaluate the presence and type of urinary dysfunction is urodynamic study by means of flowmetry [20].

The rationale for our study is the belief that the dissection routefrom the IMV to the IMA can improve nerve preservation of the nerves. The reason is anatomical, because this approach route follows the plane of dissection of the peritoneal sheets of the retroperitoneum, favoring visualization (and therefore a better preservation) of the pelvic autonomic nerves from their origin.

We hope that our study will show that the approach from the IMV to the IMA can increase the preservation of the pelvic autonomic nerves, and can thuslower the rates of sexual dysfunctionto a figure around 20%.

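### The lead sentence of Surgical technique puts an IMV-to-IMA-type splenic release before the randomized step in both arms, while the control steps put the artery first

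*Protocol article*

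**What the plan says.** Four parts of the protocol article bear on this point.

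- **Surgical technique, lead sentence.** When splenic release is needed, the reference-15 "technique is applied [15], with the subsequent dissection of the IMA according to the randomization schedule". The sentence introduces both arms and carries no arm restriction.
- **Surgical technique, arm-specific steps.** In the intervention group, "Release of the splenic angle is followed by medial to lateral dissection from the IMV to the IMA". In the control group the steps run from direct IMA dissection to high ligation, and then "The medial-to-lateral dissection proceeds, as far as the dissection of the splenic angle mobilization".
- **Background and Discussion.** Background describes the reference-15 method as a splenic flexure release "in which a dissection of the mesenteric vessels is performed from the inferior mesenteric vein (IMV) to the IMA", and says that this route "improves the visualization of the pelvic autonomic nerves from their origin". The Discussion gives the anatomical reason: "this approach route follows the plane of dissection of the peritoneal sheets of the retroperitoneum".
- **Analysis of patients by intention to treat, per protocol, and patients lost.** Intention to treat covers everyone randomized. The per-protocol set takes only part of the direct-dissection group but the whole of the IMV-to-IMA group. The Statistical analysis section runs the main comparison in both sets.

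**The concern.** The trial compares two routes to the artery, so the operative text has to keep them apart. The only splenic release method that the article names is one that it elsewhere describes by the experimental route, and the lead sentence places it ahead of the randomized step. The control steps give the opposite order. A surgeon with a control patient who needs release cannot follow both, and the five operating surgeons might resolve the conflict differently.

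The article credits the benefit to the plane of dissection. If that plane is opened in a control before the artery is approached, part of the proposed mechanism may reach the comparator. The intention-to-treat difference would then shrink, and a null result would be harder to interpret. The per-protocol comparison would be of limited help, because its two arms are selected by different rules.

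**Working it through.** **1. The texts side by side**

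| Place in Surgical technique | Order |
|---|---|
| Lead sentence, either arm, if release is needed | splenic release, then IMA dissection as randomized |
| Intervention steps | splenic release, then IMV to IMA, then high ligation |
| Control steps | direct IMA dissection, high ligation, then up to the splenic angle |

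The lead sentence agrees with the intervention steps and conflicts with the control steps. That much needs no outside source. How much of the IMV-to-IMA plane a borrowed splenic release would open is not stated.

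**2. The plan's own sample size**

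Inputs from Sample size: control risk 0.50, intervention risk 0.20, one-sided alpha 0.05, power 90%.

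Pooled-variance formula: n = [z(0.95)·√(2·p̄·q̄) + z(0.90)·√(p1q1 + p2q2)]² / d², with p̄ = 0.35, q̄ = 0.65 and d = 0.30.

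n = [1.645·√0.455 + 1.282·√0.41]² / 0.09 ≈ 41.4, or 42 rounded up. The unpooled version gives 40. The stated 41 is reproduced within one patient. Adding 10% loss gives 41/0.9 = 45.6, against the stated 45 per group.

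**3. What carry-over would do**

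Let f be the share of controls affected and e the share of the benefit that reaches them. The article gives neither, so both are assumptions.

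Control risk = 0.50 − 0.30·f·e

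Expected difference = 30 points × (1 − f·e)

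Power = Φ{[d·√n − z(0.95)·√(2·p̄·q̄)] / √(p1q1 + p2q2)}, with n = 41 per group and d, p̄ and q̄ recalculated for each control risk.

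| f·e | Control risk | Difference (points) | Power |
|---|---|---|---|
| 0 | 0.500 | 30.0 | 89.7% |
| 0.05 | 0.485 | 28.5 | 87.0% |
| 0.10 | 0.470 | 27.0 | 83.8% |
| 0.15 | 0.455 | 25.5 | 80.2% |
| 0.20 | 0.440 | 24.0 | 76.1% |

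Power reaches 80% at f·e ≈ 0.152 (control risk 0.454). The break-even share of controls is f = 0.152/e:

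- e = 0.50: f = 0.30
- e = 0.25: f = 0.61
- e = 0.15: f = 1.01, so power stays at or above 80% even if every control is affected.

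**The case against.** The strongest reply is that this is loose wording in a condensed article and that the arm-specific steps already settle the matter. Much of that stands.

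- **The intervention text separates the two steps.** If release already contained the IMV-to-IMA dissection, naming that dissection as the next step would be redundant. This supports the narrow reading, in which the splenic release is shared and only the route to the artery is randomized. A reader might infer that nothing in the section limits what is borrowed from reference 15. The intervention text does not support that inference.
- **The control steps already imply artery first.** The requested clarification therefore confirms one of two orders already on the page. It is still needed, because the lead sentence gives the other order.
- **The description of the method is one sentence in Background.** It covers the published technique as a whole and does not say which part is borrowed. Only possible carry-over can be claimed.
- **A common release method can be defended as standardizing a co-procedure.** That is a fair design preference, and the fix below gives some of it up.
- **The per-protocol wording does not mention splenic release.** It is a separate weakness and does not make the sequence conflict worse. It matters here because it is where departures from the allocated route would be handled.
- **Operations are recorded for independent grading of nerve injury.** That review is not aimed at route, but the recordings might show it.

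What the reply does not remove is the conflict between the two orders within one section.

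**Conclusion.** The point holds as an inconsistency in operative sequence, with possible partial carry-over to controls who need splenic release. Clarifying it is a cheap improvement to the plan.

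The size of any dilution is unknown, because f and e are both assumed. If the experimental route helps as hypothesized, carry-over can only move the intention-to-treat difference towards zero. At modest values the loss of power is small.

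Three stronger conclusions might be drawn, and the document supports none of them:

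- **That controls cross over to the experimental arm.** The IMA step stays randomized, and Table 2 places the risk to the superior hypogastric plexus at "Dissection and ligature of IMA". Full carry-over (e = 1) is therefore not claimed.
- **That the trial is underpowered.** This would need f·e above about 0.152, and the document gives no figure for either factor.
- **That a positive result would be suspect.** Dilution works against the hypothesis, so type I error is not raised and a positive finding is not explained away.

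**What to change.** 1. **Surgical technique.** State that in controls the IMA is dissected directly and ligated first, and that any splenic release follows without using the IMV-to-IMA route. Reword the lead sentence to match.
2. **Surgical variables.** Alongside "Type of surgical technique (LAR, NOTES-hybrid), surgical time", record in both arms the route actually used and, if convenient, whether splenic release was done. This is minor detail that may already be on the case report form.
3. **Per-protocol set.** Replace the unequal selection of the two groups with one rule based on the route received, applied identically to both arms. Keep intention to treat as randomized.
4. **Conclusion.** Describe the result as that of the approach as a package, because splenic release is a stated step of the intervention arm and may differ from controls.

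The cost is a few sentences and one or two data fields. There are two downsides: a small constraint on operative sequence in controls, and a possible difference in splenic release between arms, so that the result no longer isolates the route to the artery. The sample size stays as it is.

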### Follow-up

The patient will be referred again to the urologist to repeat the genitourinary dysfunction study 12 months after surgery: Doppler ultrasound of the penis, baseline flowmetry, EHS and the IIEF-5, I- PSS, ICIQ-SF and EORTC-QLQ C30 questionnaires.

### Study variables

#### Main variable

Preoperative, post-neoadjuvant and postoperative sexual dysfunction at 12 months in all intervened patients will be determined by the urologist, based on the results of the IIEF-5 questionnaire and/or Doppler ultrasound (peak systolic velocity, tele-diastolic velocity and response to vasodilator agent). Scores of 21 or below on the IIEF-5 questionnaire will be taken to indicate sexual dysfunction. The ultrasound will confirm or rule out the presence of sexual dysfunction generated by the test: an adequate response to thevasodilator agent, with blood flow above 35 cm/s in a patient with an altered IIEF-5 or EHS test will be considered a diagnostic criterion for ED of a neurogenic cause.

#### Secondary variables

Preoperative, post-neoadjuvant and postoperative erection hardness at 12 months;Preoperative, post-neoadjuvant and postoperative urinary dysfunction at 12 months, determined based on the results of the ICIQ-SF, IPSS and baseline flowmetry questionnaires (maximum urine volume, maximum flow, mean flow and urination time) with postvoid residue (mL). The presence of urinary dysfunction will be suspected if the patient has a score of 1 or aboveon the ICIQ-SF questionnaire, a score of 7 or above in the IPSS questionnaire or alterations in the flowmetry parameters: a maximum flow below 15 mL/s, a urinary volume less than 150 mL and/or a postvoid residue greater than 20% will be considered abnormal.Quality of life post-neoadjuvancy and 12 months after surgery will be assessed using the EORTC QLQ-C30 questionnaire.Visualization and preservation of the SHP, hypogastric nerves, the IHP and the neurovascular bundle of Walsh, during surgery (for each of these nerves), classified into: a) visualization and preservation of the nerves; b) visualization but no preservation; c) no visualization. This variable will be determined by the surgical team that performs the procedure. It will be taken into account that some patients may need the nerve resection for oncological purposes. The intervention will be recorded so that a surgeon not participating in the procedure can classify the nerve injury, as described above, and independently from the main surgeon. If there is disagreement between the two surgeons, the evaluation of a third external reviewer will be requested.

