### Statistical analysis

#### Sample size

With an α risk of 0.05 (5%), a one-sided hypothesis and a βriskof 0.1 (power of 90%), taking into account that the prevalence of post-TME sexual dysfunction is 50% and intending to reduce the figure to 20%,it will be necessary to include 41 patients in the two groups. Estimating a possible loss to follow-up of 10%, the total sample required will be 90 patients: 45 per group.

In our hospital rectal surgery for cancer is expected between 60 and 70/year, with inclusion criteria, we think that about 45–50 could be included. That means, that probabibly in two years, the recruitment should be finished.

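### A voided volume under 150 mL alone is enough to meet the only stated rule for suspected urinary dysfunction, so bladder filling on the test day can create cases in a secondary outcome

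*Protocol article*

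**What the plan says.** The Secondary variables section of the protocol article says that urinary dysfunction is "determined based on the results of the ICIQ-SF, IPSS and baseline flowmetry questionnaires", together with postvoid residue. It is to be suspected when the ICIQ-SF score is 1 or more, or when there is "a score of 7 or above in the IPSS questionnaire or alterations in the flowmetry parameters". Three alterations are listed: a maximum flow below 15 mL/s, and then "a urinary volume less than 150 mL and/or a postvoid residue greater than 20% will be considered abnormal".

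The Trial interventions section describes the test: "For the urodynamic study a flowmetry will be performed, recording: maximum urine volume (mL), maximum flow (mL/s), average flow (mL/s") and urination time, followed by an ultrasound measurement of residue. The Follow-up section has the urologist "repeat the genitourinary dysfunction study 12 months after surgery", including flowmetry.

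The Discussion gives the test particular weight, calling it "the only method able to objectively evaluate the presence and type of urinary dysfunction is urodynamic study by means of flowmetry".

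For sexual dysfunction, the Main variable section adds a second step in which the Doppler ultrasound confirms or rules out the questionnaire result. No such step is given for urinary dysfunction.

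**The concern.** Voided volume differs in kind from the other criteria. The questionnaires, the flow rate and the residue are each meant to reflect how the man stores or empties urine. The volume of a single void also depends on how much was in the bladder when the test began. A man who emptied his bladder shortly before the visit will pass little, whatever his function. The rule counts that as a positive finding.

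If maximum flow also tends to be lower in small voids, one under-filled test could trip two criteria at once, for example 100 mL passed at 12 mL/s with no residue. The article does not state that dependence, so it is an assumption here, to be confirmed by the trial's urologists. The main point does not need it.

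Urinary dysfunction is the first secondary objective listed in the Objectives section, and it is part of the genitourinary hypothesis. Misclassification unrelated to the dissection route would overstate the reported rates and make a real difference harder to see.

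**Working it through.** **1. Logic of the rule.** Write the rule as stated:

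Suspected dysfunction = (ICIQ-SF ≥ 1) OR (IPSS ≥ 7) OR (maximum flow < 15 mL/s) OR (volume < 150 mL) OR (residue > 20%).

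Take a man with ICIQ-SF 0, IPSS below 7, maximum flow of at least 15 mL/s, residue of at most 20% and a void of 140 mL. Four terms are false and one is true, so he meets the rule. Flow, residue and symptoms each have their own term. The volume term therefore adds only men whose sole finding is a small void.

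**2. Comparison with sexual dysfunction.** There, a positive questionnaire is followed by a test that can overturn it. Here the suspicion rule is the only rule printed, so nothing shown removes the man in step 1.

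**3. Direction of the effect.** Let t be the true rate in an arm. Let f be the share of men without dysfunction who are added on volume alone, equal in both arms. Assume that all true cases are detected. Then

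labelled rate = t + (1 − t)f, and labelled difference = (1 − f)(t₁ − t₂).

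Both rates rise and the difference shrinks by the factor (1 − f).

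**4. Illustration only.** The article gives no expected urinary rates by arm, no power for this outcome and no f. The inputs below are assumptions:
- True rates of 30% and 12%, the upper ends of the two ranges in the Background section.
- 41 analysed per arm and one-sided 5%, borrowed from the Sample size section. That 41 belongs to the primary outcome (50% v 20%, 90% power). It is reproduced closely: 42 with the pooled normal formula, 41.4 with the arcsine formula, and power 0.897 at 41.

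Unpooled power = Φ(d/SE − 1.645), with SE = √[(p₁q₁ + p₂q₂)/41]. For f = 0, SE = √[(0.2100 + 0.1056)/41] = 0.0877. Then 0.18/0.0877 − 1.645 = 0.41, and Φ = 0.66.

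| f (assumed) | Labelled rates | Difference | Power, unpooled | Power, pooled |
|---|---|---|---|---|
| 0 | 30.0% v 12.0% | 18.0 points | 0.66 | 0.64 |
| 10% | 37.0% v 20.8% | 16.2 points | 0.50 | 0.49 |
| 20% | 44.0% v 29.6% | 14.4 points | 0.39 | 0.38 |

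**5. Limit of the illustration.** It supposes that no man without dysfunction is already labelled by another criterion. If a share g is already labelled by ICIQ-SF or IPSS, independently of volume, the difference is (1 − g)(t₁ − t₂) before volume is considered and (1 − g)(1 − f)(t₁ − t₂) after. The points lost to volume are then f(1 − g)(t₁ − t₂), which is less than the table shows. The article gives no g either.

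**The case against.** Several objections have force.

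- **The word is *suspected*.** A reader might infer that every under-filled bladder is recorded as dysfunction. The text does not say that, and the urologist may exercise judgement. This stands as a limit on wording. The printed rule is still the only one given, and no step for removing a suspected case is described.
- **Test conduct.** A reader might infer that the trial takes one void with no filling condition and no repeat. That rests on the silence of a condensed article, and such detail may sit in the full protocol or the unit's procedures. This stands, and the point does not depend on it. What the article does state is that a low volume is abnormal. Good filling practice would make the problem rarer without correcting the rule.
- **A small void can be real.** The Definitions section includes altered storage, and these men have had pelvic chemoradiotherapy and surgery. Nor does the article call 150 mL a validity threshold. This stands in part: dropping the criterion gives up some sensitivity. A single volume cannot separate low capacity from low filling, whereas the questionnaires address symptoms directly.
- **Size.** A reader might take the power figures as the trial's loss. They are not. The rates, f and the absence of other false positives are all assumed, and the trial was not sized for this outcome.
- **Bias.** A reader might infer a false benefit for one arm. Allocation is random, and patient and urologist are blinded, so dilution is the expected effect.

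**Conclusion.** The point holds as a fault in a stated outcome definition. A void under 150 mL alone meets the only rule printed for suspected urinary dysfunction, although it may reflect filling and not function. The expected consequence is non-differential false positives, with higher rates in both arms and a difference reduced by the factor (1 − f). This rests on three premises: volume depends on filling, under-filling is unrelated to allocation, and the suspicion rule is what will be analysed.

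The amount cannot be derived from the article. The consequence is confined to one secondary outcome, and the primary outcome and the sample size are untouched. This is a minor but inexpensive correction.

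**What to change.** In Secondary variables, remove volume under 150 mL as a stand-alone abnormal criterion. State that a flow test below 150 mL is not evaluable for maximum flow and that the void is repeated at the same visit where feasible. Classify on evaluable maximum flow, residue, ICIQ-SF and IPSS, in the same way before surgery and at 12 months. Say how a suspected case becomes the analysed outcome. State what the 20% residue is a percentage of. If it is relative to volume, it too may be unstable in a small void, and the text should say how it is read there.

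Report voided volume descriptively by arm and add a sensitivity analysis under the rule as now printed. The components are recorded separately, so this needs no new variables.

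The cost is an edit to the definition and an occasional longer visit. A man whose bladder truly holds little would be detected only through the questionnaires or in the sensitivity analysis.

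### Nerve visualisation and preservation, a secondary variable, is scored by raters who are not masked to arm; the planned video check makes the raters independent of each other but does not hide the randomised route

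*Protocol article*

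**What the plan says.** The Secondary variables section classifies each of four structures (SHP, hypogastric nerves, IHP, neurovascular bundle of Walsh) as visualised and preserved, visualised but not preserved, or not visualised.

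- **First rater:** "This variable will be determined by the surgical team that performs the procedure".
- **Second rater:** "The intervention will be recorded so that a surgeon not participating in the procedure can classify the nerve injury". This is done "independently from the main surgeon".
- **Third rater:** "If there is disagreement between the two surgeons, the evaluation of a third external reviewer will be requested".

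The Blinding section reads: "Neither the patient nor the urologist performing the sexual and urinary function study will have access to any surgical data". It adds that these two do not know the arm, and it names nobody else. The article does not say that the recording is cut or coded, or that the second or third rater is kept unaware of the arm.

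**The concern.** The three categories call for judgement. The first rater knows the arm and is judging its own dissection. The second can see the arm on screen. The Background and the Discussion both state the expectation that the route from the inferior mesenteric vein (IMV) to the inferior mesenteric artery (IMA) gives better visualisation and preservation, so the likely direction of any rating bias is towards the intervention.

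The Hypothesis section runs from dissection route to nerve preservation to less genitourinary dysfunction, and the Discussion places better visualisation before preservation. This variable is the trial's direct measure of that middle step. If it favoured the intervention, the result could not be separated from the raters' expectation. The support it would lend to the mechanism would be weaker than it looked.

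**Working it through.** **1. What the recording reveals.** Surgical technique describes the two arms by a visible difference. Control: "Control group, with direct dissection of the IMA". Intervention: "Release of the splenic angle is followed by medial to lateral dissection from the IMV to the IMA". Where the splenic flexure has to be released, the same technique may be used in either arm, but the IMA dissection that follows still goes by the randomisation. An unedited recording therefore lets its viewer infer the arm.

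**2. What the three reads protect against.** An unjustified upgrade by the operating team meets one of two situations:

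- The second surgeon disagrees. The third reviewer is called, and the upgrade stands only if that reviewer sides with the operator.
- The second surgeon agrees. The score stands and no third read takes place.

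The scheme catches an operator's individual error. It cannot catch an expectation held by both raters.

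**3. Which nerves could be read without the route in view.** After the vessel step both arms share one sequence: "The surgery continues with the following standardized steps". Setting Table 2 beside Surgical technique gives:

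| Structure | Risk area in Table 2 | Where it falls in Surgical technique |
|---|---|---|
| SHP | Dissection and ligature of the IMA | Vessel step, which differs by arm |
| Hypogastric nerves | Posterior dissection | Common steps, but also separated laterally within the control-arm vessel step |
| IHP | Lateral dissection | Common steps |
| Bundle of Walsh | Anterior dissection | Common steps |

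Only the last two can be read fairly from footage that starts at the common steps.

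**4. Size, for illustration only.** The protocol gives no expected preservation rate and no misclassification rate. Its only sample-size figure is for the primary endpoint: 41 per group, 45 after losses. The usual normal approximation gives 42 pooled or 40 unpooled, so 41 is in line. Only the 45 per group is used below.

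Assumptions: no true difference; true preservation *p* in both arms; a fraction *q* of non-preserved intervention cases is upgraded in the final score, and none in control; the variable is reduced to preserved or not.

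- Patients reclassified = 45 × (1 − p) × q
- Apparent rate in the intervention arm: p₂ = p + (1 − p)q, so the spurious gain is (1 − p)q
- Chance of a significant result favouring the intervention = Φ{[(p₂ − p)√45 − z√(2p̄(1 − p̄))] / √[p(1 − p) + p₂(1 − p₂)]}, where p̄ is the mean of p and p₂

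Example, p = 0.6 and q = 0.3: 45 × 0.4 × 0.3 = 5.4 patients; p₂ = 0.72; p̄ = 0.66. With z = 1.96, (0.12 × 6.708 − 1.96 × 0.670)/0.665 = −0.76, and Φ = 0.222.

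| p | q | Reclassified of 45 | Gain (points) | Two-sided 0.05 (nominal 2.5% in this direction) | One-sided 0.05 (nominal 5%) |
|---|---|---|---|---|---|
| 0.6 | 0.1 | 1.8 | 4 | 5.8% | 10.5% |
| 0.6 | 0.2 | 3.6 | 8 | 12.0% | 19.6% |
| 0.6 | 0.3 | 5.4 | 12 | 22.2% | 32.7% |
| 0.7 | 0.1 | 1.4 | 3 | 5.0% | 9.2% |
| 0.7 | 0.2 | 2.7 | 6 | 9.3% | 15.7% |
| 0.7 | 0.3 | 4.1 | 9 | 16.2% | 25.2% |
| 0.8 | 0.1 | 0.9 | 2 | 4.3% | 8.0% |
| 0.8 | 0.2 | 1.8 | 4 | 7.1% | 12.5% |
| 0.8 | 0.3 | 2.7 | 6 | 11.4% | 18.7% |

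**The case against.** **The safeguard is real.** A recording, an independent second read and external adjudication are planned, and an operator's wrong upgrade does not pass on its own. This stands and limits the concern. It does not remove it, because the protocol promises independence from the operator's score and not ignorance of the arm.

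**The article is condensed.** The full protocol may describe how clips are handled, and silence is weak evidence that nothing is masked. This stands in part. In particular, the article does not say what material the third reviewer sees, so a reader might infer that every assessor knows the arm, but the text does not establish that. It does fix who rates, from what source, and when adjudication starts, and as written that rule leaves the first two raters unmasked.

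**The trial's conclusion does not depend on this variable.** Correct. A reader might infer that the main result is biased or that this is a key endpoint. The documents support neither: it is listed as an ordinary secondary variable, and sexual dysfunction is determined by the blinded urologist.

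**A larger bias is easy to assume.** Applying a 10-20% upgrade to all 45 intervention patients would give 4.5 to 9 patients and a gain of 10-20 points. Only non-preserved cases can be upgraded, however. At 80% preservation there are 45 × 0.2 = 9 of them, so a 20-point gain would require upgrading every one.

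**Clips cut after the vessel step would lose relevant footage.** This holds for the hypogastric nerves, which the control arm already handles in the vessel step. Starting later would drop control-arm footage in which they could be injured, and so could create a bias of its own. The same cut also removes the segment closest to the claim that the nerves are seen from their origin.

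**Conclusion.** The concern holds as a limited one. The rating rule for nerve visualisation and preservation makes the raters independent of each other but does not mask them to arm, and a bias shared by the first two is never adjudicated. It is a risk, not a demonstrated effect, and the primary endpoint is untouched.

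Its size is unknown. On the assumed values above, about 1-5 of 45 patients per nerve would be reclassified, a gain of 2-12 points. The chance of a false finding for the intervention would be about 4-22% at two-sided 0.05 (nominal 2.5% in that direction), or 8-33% at one-sided 0.05 (nominal 5%). These ranges rest wholly on the assumed preservation and upgrade rates, and on the upgrades surviving the second read.

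The variable carries the mechanism of the hypothesis and the improvement is cheap, so the change is worth making for the two structures where it can work.

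**What to change.** **IHP and bundle of Walsh.** Give the outside surgeon and the third reviewer, both already planned, coded clips that start at the steps common to both arms. Supply neither the arm nor the operating team's score. Analyse the outside surgeon's masked reading. Keep the operating team's score and the adjudicated score as supportive results, and report agreement between raters.

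**SHP and hypogastric nerves.** Keep the full recording and the present scheme. Report these two separately and label the readings as not blinded to arm.

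**Protocol text.** Extend the Blinding section to say which raters are masked, for which nerves, and from what material.

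**Cost.** Minor editing and coding of recordings the trial already makes, and a short protocol change. The clips lose some context, the later operative field may still hold cues to the route, the analysed value for the masked nerves rests on one reader, and two of the four structures stay unmasked.
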